### Assessment of anthropometric parameters

The patients' height is calculated based on the ulna length due to limitations in the ICU (28):

The patients' weight is calculated based on MAC and Calf Circumference due to limitations in the ICU (29):

### Method of measuring calf circumference

In the supine position, the patients’ leg muscle circumference is measured. The left knee of the patient rises high enough to form a right corner between the thigh and the leg. The tape is placed around the leg muscle and is moved along the muscle to measure the largest circumference without applying pressure to the subcutaneous tissue (Kangalgil et al. 2022).

### Assessment of 28-day mortality

The follow-up of 28-day mortality will be done by phone. 

### Assessment of the level of GCS

Patients' levels of consciousness (GCS) will be extracted from hospital records.

### Evaluation of clinical outcomes

To evaluate the clinical outcomes before and after the intervention, the Acute Physiology and Chronic Health Evaluation II (APACHE II), the Sequential Organ Failure Assessment (SOFA), and the NUTRIC Score will be evaluated (Kalaiselvan et al. 2017; Qiao et al. 2012). To eliminate potential human errors in the calculation of these scores, these scores will be measured by a questionnaire and automatically calculated by a web-based system.

### Laboratory assessment

At the beginning and end of the trial, blood will be drawn. Blood will be collected at 6:00 am before the first gavage to evaluate the serum levels of inflammatory factors (CRP, ESR, IL-6, IL-18, and TNF α), CBC, LDH, and oxidative stress indicators (MDA, catalase, GPx, SOD and TAC). As soon as the blood samples are collected, they will be centrifuged at 3600 rpm, the serum will be separated from the sediment, and it will be preserved at -80°C. Oxidative stress factors will be measured calorimetrically using a commercial diagnostic kit. Measurements of inflammation will be conducted using ELISA kits based on dual biotin antibody sandwich technology. Commercial diagnostic kits will also be used to measure CBC and LDH.

### Statistical methods

SPSS version 22 (SPSS Inc., Chicago, IL, USA) will be used to perform the analysis. For quantitative data, mean and standard deviation (SD) will be reported, and for qualitative data, frequency and percent will be reported. Kolmogorov-Smirnov test will be used to determine whether variables had a normal distribution (Ahad et al. 2011). Paired t-test will be applied to evaluate the differences in each group before and after the intervention. Independent t-test will be used to show the baseline and endpoint differences between the two groups. The Kruskal Wallis test will be used for the between-groups comparison, and the Wilcoxon Ranked Sum test for the inter-group comparisons, if the distribution of data is not normal. We will apply analysis of covariance (ANCOVA) to show differences between two treatment groups after adjusting for confounding variables. For missing data, an intention-to-treat analysis will be performed (Herman et al. 2009). Statistical significance is defined as a p-value less than 0.05.

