### Randomization

Study participants who meet the inclusion criteria will be enrolled. A random number generator website will be used to randomly assign patients to intervention or control groups: https://www.sealedenvelope.com/simplerandomiser/v1/lists. Patients will be randomized into intervention or control groups with a block size of four (1:1). At randomization, individuals will be stratified by GCS (3 to 8 and 9 to 13) and age (18 to 50 and 51 to 80) so that these variables will be equally distributed between the two groups. The sequence of allocation will be determined by permuted blocks of four. A block size of four creates six different blocks for assigning patients to the trial groups. There will be identical packets and labels for intervention and placebo, each with its own sequence number. One of the investigators who is not involved in patient care will generate the allocation sequence number.

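### Several tests are planned for each continuous outcome with none named primary, and neither the endpoint t-test nor the ANCOVA is tied to the baseline value and the randomisation strata

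*Protocol article*

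**What the plan says.** The Statistical methods section of the protocol article lists these analyses for quantitative outcomes:

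- Within each arm: "Paired t-test will be applied to evaluate the differences in each group before and after the intervention".
- Between arms, unadjusted, at two time points: "Independent t-test will be used to show the baseline and endpoint differences between the two groups".
- If the data are not normal, rank tests instead: "The Kruskal Wallis test will be used for the between-groups comparison", with a Wilcoxon test named as well.
- Between arms, adjusted: "We will apply analysis of covariance (ANCOVA) to show differences between two treatment groups after adjusting for confounding variables".

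One threshold covers all of them: "Statistical significance is defined as a p-value less than 0.05". The section does not say which analysis decides the result, and it does not list the ANCOVA covariates.

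Two other parts of the article bear on this. Under Randomization, "individuals will be stratified by GCS (3 to 8 and 9 to 13) and age (18 to 50 and 51 to 80", in permuted blocks of four at 1:1. Under Outcome assessment and in Table 1, every biochemical marker is measured on day 1 and day 7. The baseline value and both strata are therefore on file for each randomised patient. The sample size section treats CRP as the main outcome.

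**The concern.** Three features of the plan work against a clear answer.

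1. **Lost precision.** The unadjusted endpoint comparison ignores the baseline value of the same marker, which is often a strong predictor of the day-7 value, and ignores the factors used to stratify allocation. The ANCOVA could use them, but the article describes its covariates only as confounders.
2. **No order of precedence.** The t-test and the ANCOVA address the same between-arm question and will sometimes disagree. If either may be reported as the result, the false-positive rate exceeds 5%.
3. **Tests that do not compare the arms.** A paired test asks whether one arm changed. Both arms receive standard sepsis treatment, so markers may move over seven days without any saffron effect. A significant change in one arm beside a non-significant change in the other can then be read as a treatment effect. The baseline t-test, for its part, tests a hypothesis that randomisation already makes true.

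**Working it through.** **Inputs from the protocol:** alpha 5%, power 80%, 35 per arm before attrition, Δ = 3 for CRP, 1:1 allocation. **Not stated:** SD, sidedness, baseline-to-day-7 correlation r, and any change common to both arms. I assume two-sided tests, normal data and r = 0.3, 0.5 or 0.7.

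**1. The plan's own sample size.** With no SD, 35 per arm cannot be reproduced, only solved backwards.
- Normal approximation: d = (1.960 + 0.842) × √(2/35) = 0.67, so SD = 3/0.67 ≈ 4.48.
- t distribution, 68 degrees of freedom: d = 0.68, so SD ≈ 4.42.
- One-sided: d would be about 0.59.

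The 80% for the endpoint t-test below is therefore true by construction. Only the gain over it is informative.

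**2. Precision.** Adjusting for baseline multiplies the residual SD by √(1 − r²), so the standardised effect becomes 0.679/√(1 − r²). The number per arm for 80% power becomes 35 × (1 − r²).

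| r | √(1 − r²) | Effect | ANCOVA power, 35 per arm | n per arm for 80% |
|---|---|---|---|---|
| 0.3 | 0.954 | 0.712 | 84% | 32 |
| 0.5 | 0.866 | 0.784 | 90% | 27 |
| 0.7 | 0.714 | 0.951 | 98% | 18 |

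Simulation, which also pays for estimating the baseline slope, gives 83%, 89% and 97%. If all 45 per arm were analysed, the t-test would have 89% power and the ANCOVA about 92%, 96% and 99%.

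**3. Choosing between two tests.** I simulated trials with 35 per arm (40,000 per setting).

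| r | No effect: t-test alone | No effect: ANCOVA alone | No effect: either < 0.05 | 0.68 SD effect: verdicts differ |
|---|---|---|---|---|
| 0.3 | 5.1% | 5.3% | 6.6% | 7% |
| 0.5 | 4.9% | 4.9% | 7.1% | 13% |
| 0.7 | 5.0% | 5.2% | 8.4% | 18% |

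Each test alone holds its level. Smaller simulations (4,000 runs per setting) gave 5.6% to 8.7% for either test, so about 6% to 9% per marker is a fair summary.

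**4. Within-arm tests.** Suppose both arms truly shift by the same amount δ (in SD units). The SD of the change is √(2(1 − r)), which equals 1 at r = 0.5. Let p be the power of one paired test with 35 patients. The chance of significance with saffron but not with placebo is p(1 − p). At r = 0.5:

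| δ | p | p(1 − p) |
|---|---|---|
| 0 | 0.050 | 4.8% |
| 0.3 | 0.407 | 24.1% |
| 0.5 | 0.820 | 14.8% |
| 0.8 | 0.996 | 0.4% |

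The ceiling for any δ and r is 25%, reached at p = 0.5. Doubling the column gives the chance of a split in either direction (48% at 0.3 SD, 30% at 0.5 SD), but only half of those splits favour saffron.

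**The case against.** **A condensed article may leave the covariate list and the choice of primary model to a fuller document.** This stands as far as the missing list goes, and the word confounders may be meant to include the baseline value. The point rests instead on what the article does state: parallel tests at one threshold, significance tests at baseline and within arms, and an unadjusted endpoint comparison where a better one costs nothing.

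**An adjusted between-arm analysis is already planned.** True. It would be wrong to infer that the raw t-test is the only between-arm comparison. What remains is that the ANCOVA is neither primary nor tied to the baseline value and strata.

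**The unadjusted test is valid.** Also true. A reader might infer that the planned analysis is biased or fails to control error. It is not: under 1:1 randomisation the endpoint t-test holds about 5%, and the loss is one of precision, only about 4 percentage points of power at r = 0.3.

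**Misuse is not announced.** A reader might infer that covariates will be picked from the baseline tests, or that a significant paired test will count as efficacy. The article says neither. It gives the paired tests the limited purpose of describing change within each arm. The risk is one of interpretation.

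**The magnitudes rest on assumptions.** They do. The effect size is back-solved, the correlations and common shifts are assumed, and the 6% to 9% presumes an ANCOVA that adjusts for baseline.

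**Conclusion.** The point holds as a should-fix. The article plans several tests for each continuous outcome, ranks none of them, and does not commit any between-arm analysis to the baseline value or to the GCS and age strata.

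Its size is moderate. The precision forgone runs from small (r = 0.3) to substantial (r = 0.7). The either-test inflation is modest for a single marker. The chance of a misleading saffron-only change depends heavily on the unknown common shift: it peaks near 25% at intermediate shifts and falls below 5% when there is no shift or a large one. The further gain from adding the strata cannot be quantified, because the document gives no relation between GCS or age and the markers. None of this makes the planned endpoint comparison invalid.

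**What to change.** Name one primary analysis: an ANCOVA of day-7 CRP (log scale if skewed, decided in advance) on arm, baseline CRP, GCS stratum (3–8 or 9–13) and age stratum (18–50 or 51–80), reporting the adjusted difference with its 95% confidence interval. Use the same model for the other continuous markers and scores. Report within-arm changes descriptively, without p-values, and replace the baseline significance tests with a descriptive table. If the endpoint t-test is kept, label it supportive.

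The cost is wording only. All the variables are already collected and SPSS fits the model. The change should be made before treatment codes are opened.

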## Materials and Methods

This study protocol was developed following the Standard Protocol Items: 

Recommendations for Interventional Trials (SPIRIT) 2013 checklist (Chan et al. 2013). It is a randomized, parallel, two-arm, double-blinded, and placebo-controlled clinical trial that will include 90 critically ill patients with sepsis. Figure 1 illustrates the trial design. From May 2024, patients will be selected from the ICU of Al-Zahra Hospital, an academic hospital affiliated with Isfahan University of Medical Sciences, Isfahan, Iran. We will screen subjects according to our inclusion and exclusion criteria before including them in the study. 

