### Power calculation and sample size estimates

Using the formula for randomized clinical trials, the sample size was calculated considering type I error at 5% and type II error at 20% (β = 0.2; power = 80%). CRP level was considered a main outcome, and based on a previous study, the sample size was calculated to be 35 persons for each group (Δ = 3) (Rai et al. 2017). Considering attrition, 90 patients will be considered in total, 45 in each group.

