### Outcome assessment

Our primary outcomes will be serum levels of CRP, TNF-α, IL-6, IL-18, and ESR as a marker of inflammation, serum LDH as an indicator of cell damage, TAC, SOD, GPx, MDA and catalase as an indicator of oxidative stress that will be measured at the beginning and end of the study. In addition, the 28-day mortality rate, GCS, CBC, APACHE II Score, SOFA score, and NUTRIC score are secondary outcomes. Anthropometric variables including weight, height, body mass index (BMI), and calf circumference will be assessed at baseline of the study (Table 1). Mid arm circumference (MAC) will be assessed at baseline and end of the study. 

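### The non-normal fallback names the same between-arm test twice and gives no paired rank test for the before/after comparison

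*Protocol article*

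**What the plan says.** The design is stated under Materials and Methods: "It is a randomized, parallel, two-arm, double-blinded, and placebo-controlled clinical trial that will include 90 critically ill patients with sepsis". Under Outcome assessment, the eleven primary markers (CRP, TNF-α, IL-6, IL-18, ESR, LDH, TAC, SOD, GPx, MDA and catalase) are ones "that will be measured at the beginning and end of the study". Table 1 places the biochemical assays at days 1 and 7, so each patient contributes a pair of values.

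Statistical methods first sets the switch: "Kolmogorov-Smirnov test will be used to determine whether variables had a normal distribution". Normally distributed markers get a paired t-test within each arm and an independent t-test between arms, at baseline and at the endpoint. For other markers: "The Kruskal Wallis test will be used for the between-groups comparison, and the Wilcoxon Ranked Sum test for the inter-group comparisons". A separate sentence then applies ANCOVA to the two arms, adjusting for confounders that are not listed. No signed-rank test or other paired rank test is named anywhere.

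**The concern.** The rule for normal data covers two comparisons, one within arms and one between arms. The fallback should mirror both. It names two tests instead, each of which is for independent samples, and the two labels it attaches to them both mean between groups.

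There are two ways to read it:

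- **Literally**, the between-arm comparison is specified twice and the within-arm comparison has no test for non-normal data.
- **As the counterpart of the paired t-test** (intra-group intended), a test that assumes independent samples would be run on two measurements from the same patients. It ignores the pairing and misstates the variance of the difference.

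Inflammatory markers in septic ICU patients may well be skewed, so the fallback could be used for several primary markers. At stake is whether the before/after p-values for those markers mean what they say.

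**Working it through.** **The plan's own figure.** The only stated number nearby is 35 per group for CRP with Δ = 3, 5% type I error and 80% power (Power calculation and sample size estimates). No SD is given, so it cannot be reproduced independently. With n = 2(1.960 + 0.842)²·SD²/Δ² (two-sided, assumed), SD 4 gives 28, SD 4.45 gives 35 and SD 5 gives 44. An SD of about 4.42 to 4.48 is implied. The point here does not depend on that figure; 35 is used below as the number of pairs per arm.

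**Step 1: are the two named tests different?** With two groups, the Kruskal-Wallis statistic is the square of the standardised rank-sum statistic. On one simulated data set of 35 against 35 log-normal values, the p-values were 0.3384 for Kruskal-Wallis and 0.3384 for rank-sum without continuity correction. They are one test.

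**Step 2: rank-sum applied to pairs.** The documents give no pre/post correlation r, so 0.3, 0.5 and 0.7 are assumptions. Log-normal markers, 35 pairs, 10,000 simulated trials per setting, nominal two-sided 5%:

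| Assumed r | True size, rank-sum | True size, signed-rank (log) |
|---|---|---|
| 0.3 | 1.9% | 4.3% |
| 0.5 | 0.8% | 5.0% |
| 0.7 | 0.1% | 4.7% |

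A large-sample check agrees. With no change over time, pairing multiplies the variance of the rank-sum statistic by about 1 − r_S, where r_S = (6/π)·arcsin(r/2) is the rank correlation. The true size is then 2·[1 − Φ(1.960/√(1 − r_S))]:

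- r = 0.3: r_S = 0.288, 1.960/0.844 = 2.32, size 2.0%
- r = 0.5: r_S = 0.483, 1.960/0.719 = 2.72, size 0.6%
- r = 0.7: r_S = 0.683, 1.960/0.563 = 3.48, size 0.05%

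**Step 3: power for a real before/after change.** Assumed fall of 0.5 SD on the log scale, same simulations:

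| Assumed r | Rank-sum | Signed-rank, raw values | Signed-rank, log values |
|---|---|---|---|
| 0.3 | 52% | 60% | 66% |
| 0.5 | 53% | 73% | 80% |
| 0.7 | 55% | 91% | 95% |

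**Step 4: the between-arm comparison.** Rank-sum, or equivalently Kruskal-Wallis, on two independent arms is a valid test, so steps 2 and 3 do not apply to it. What baseline adjustment would add was checked separately: 35 per arm, an assumed 0.67 SD effect on the log scale, 3,000 simulated trials per setting.

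| Assumed r | Endpoint rank-sum | ANCOVA, raw skewed values | ANCOVA, log values |
|---|---|---|---|
| 0.3 | 76% | 62% | 82% |
| 0.5 | 78% | 67% | 88% |
| 0.7 | 78% | 79% | 97% |

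The scale matters. ANCOVA on untransformed skewed values does worse than the unadjusted rank test at r = 0.3 and 0.5, while ANCOVA on log values does best throughout.

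**The case against.** The strongest reply is that this is a slip of terminology. The preceding sentences define exactly two comparisons, and a reader would naturally supply signed-rank and intra-group. That is likely. But the printed rule is still wrong, and an analyst who follows it has no correct within-arm test to run.

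A second reply is that the damage is limited. This stands in full. The within-arm comparison is not the randomised contrast, so the power figures in step 3 are not lost power to detect an effect of saffron against placebo. The error also runs in the conservative direction: it hides real before/after changes and does not create false ones.

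A third reply concerns a stronger reading that a reader might infer: that the normality check decides, marker by marker, whether a comparison is adjusted for baseline, so that skewed markers lose the adjustment. The text does not support this, for three reasons:

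- The rank tests replace t-tests, and the independent t-test at the endpoint is unadjusted too.
- The non-normality condition belongs to the rank-test sentence; the ANCOVA sentence carries no such condition.
- The ANCOVA sentence never names the baseline value as a covariate.

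Finally, covariates and analysis scale are details that an article may leave to an analysis plan that is not shown. For that reason they appear below as an improvement and not as an error.

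**Conclusion.** The point holds as a definite but contained error in the stated analysis. The fallback names one independent-samples test under two names and no paired rank test. If rank-sum is used on the before/after pairs, the true size is about 1.9%, 0.8% and 0.1% instead of 5%, and power is about 52–55% against 60–91% (signed-rank, raw values) or 66–95% (log values). These figures rest on assumed correlations of 0.3 to 0.7, an assumed 0.5 SD log-scale change, log-normal markers and 35 pairs; none of the correlation, the change or the distribution is given in the article.

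The between-arm rank test is valid and the randomised comparison is not invalidated. The correction should still be made, because it is specific and costs almost nothing.

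**What to change.** **Correction.** In Statistical methods, replace the fallback sentence so that non-normal markers use the Wilcoxon signed-rank test for change within an arm and the Mann-Whitney (rank-sum) test between arms. Delete Kruskal-Wallis.

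**Improvement at little cost.** State that ANCOVA is the main between-arm analysis, with the marker's baseline value and the stratification factors from the Randomization section (GCS 3–8 or 9–13, age 18–50 or 51–80) as covariates, on the log scale for skewed markers. The endpoint t-test and the endpoint rank test are both unadjusted for baseline, so either would then be supportive only.

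**Cost.** A few lines of wording, to be settled before unblinding; no change to data collection or sample size. The one downside is that effects on log-transformed markers are read as ratios of geometric means and not as differences in the original units.

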### Exclusion criteria

Dissatisfaction of the patient or his legal guardian. Patients who stay in the ICU for <48hr. Patients receiving parenteral nutrition. Patients receiving enteral or oral nutrition initially but transferring to parenteral nutrition due to contraindications. Patients who are incapable of receiving enteral nutrition or who may not be able to receive enteral nutrition in the future as a result of incomplete resuscitation and hemodynamic instability or gastrointestinal disorders such as nausea, persistent vomiting, ileus, obstruction of the intestinal tract, diarrhea that exceeds 500 ml per day, and high-output fistulas. Cancer patients undergoing chemotherapy. Patients suffering from pancreatitis, kidney failure, or congenital or immune disorders. Patients taking phenobarbital, levetiracetam, or phenytoin. Dialysis patients, patients with severe septic shock or sepsis, or DIC (diffuse intravascular coagulation). Pregnancy and breastfeeding. Patients with BMI < 18.5 kg/m^2^. Patients who need blood transfusions frequently. Unwanted side effects associated with taking supplements or placebos. ICU patients who are expected to die within 2 days of admission. Patients who take other herbal supplements. Patients with a spice or herbal supplement allergy. Patients with GCS levels less than 3 or greater than 13. Patients who passed away during the trial

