**Placebo (100 mg corn starch)**					
**Intervention (100 mg saffron)**					
**Adverse events**					
Outcome assessment:					
**Biochemical assays**		*		*	
**Assessment of APACHI II score, SOFA score, NUTRIC score**		*		*	
**Assessment of mid arm circumference**		*		*	
**Other anthropometric variables**		*			
**Assessment of mortality**					*

APACHE II: Acute Physiology and Chronic Health Evaluation II, SOFA: Sequential Organ Failure Assessment

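### Intention-to-treat is named as the missing-data method while patients who die are excluded, so the Day-7 comparisons are survivors-only under an intention-to-treat label

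*Protocol article*

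**What the plan says.** All references are to the protocol article.

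- **Statistical methods**, on missing data: "For missing data, an intention-to-treat analysis will be performed". The article itself states no imputation rule and no rule for death.
- **Statistical methods**, on the tests: "Independent t-test will be used to show the baseline and endpoint differences between the two groups", and "We will apply analysis of covariance (ANCOVA) to show differences between two treatment groups after adjusting for confounding variables". Paired t-tests and rank tests are also planned.
- **Exclusion criteria**: "Patients who passed away during the trial". The same list contains other events that can occur only after entry, such as "Unwanted side effects associated with taking supplements or placebos" and a later change to parenteral nutrition.
- **Outcome assessment**: the primary biomarkers are outcomes "that will be measured at the beginning and end of the study". The 28-day mortality rate is a separate secondary outcome, alongside GCS, CBC, APACHE II, SOFA and NUTRIC.
- **Evaluation of clinical outcomes** and **Table 1**: the scores are taken "To evaluate the clinical outcomes before and after the intervention". Table 1 marks the biochemical assays and the row "Assessment of APACHI II score, SOFA score, NUTRIC score" at Day 1 and Day 7 only. GCS has no row in Table 1, but the Abstract places it at the start and end of the study.

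**The concern.** Two statements do not fit together, and neither deals with a patient who dies before Day 7. Intention-to-treat keeps every randomised patient in the assigned arm. A list that excludes those who die removes some of them because of something that happened after randomisation. Striking the exclusion would restore these patients to the mortality count but would not create a Day-7 value for them, so the missing-data sentence has to change as well.

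What is at stake is how the result is read. Random allocation makes the arms comparable at entry, not among those still alive a week later. If one arm loses more of its sickest patients, its survivors are a healthier selection and their mean SOFA or CRP looks better. A reader told that the analysis is intention-to-treat would not look for this.

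**Working it through.** **Step 1: does the stated rule produce a Day-7 value?** There is one post-baseline measurement, at Day 7. A patient who dies before then has none. The independent t-test, paired t-test, rank tests and ANCOVA each need an end value and leave out a patient without one. Together with the exclusion of deaths, the text gives a survivors-only comparison.

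**Step 2: the plan's own figures.** The Power calculation section gives 35 per group for a CRP difference of 3 (5% type I error, 80% power), raised to 45 for attrition. The SD is not stated, so 35 can only be inverted. If the test is two-sided:

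SD = 3 / ((1.960 + 0.842) × √(2/35)) = 4.48

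The implied attrition is 1 − 35/45 = 22.2%, or 10 patients per arm, with no split by cause. The point does not depend on these figures; they only give a scale for CRP.

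**Step 3: size of the survivor bias when treatment has no effect on severity.** Let Day-7 severity be normal and equal in both arms. A patient dies early when a trait with correlation r to severity exceeds the cut-off c that gives death rate p. The mean severity of survivors, in SD units, is then

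−r × g(p), with g(p) = φ(c)/(1 − p) and c = Φ⁻¹(1 − p).

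| p | c | φ(c) | g(p) |
|---|---|---|---|
| 10% | 1.2816 | 0.1755 | 0.1950 |
| 15% | 1.0364 | 0.2332 | 0.2743 |
| 20% | 0.8416 | 0.2800 | 0.3500 |
| 30% | 0.5244 | 0.3477 | 0.4967 |

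The false advantage of the arm with more deaths is SD × r × (difference in g). The documents give no death rates, no SOFA SD and no correlation. Assumed: SOFA mean 7, SD 3.5, r from 0.5 to 0.7. False significance comes from simulated trials of 45 per arm, survivors compared by t-test, counting two-sided p < 0.05 in favour of the arm with more deaths (nominal 2.5%).

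| Early deaths | Difference in g | SOFA points, r = 0.5 to 0.7 | False significance |
|---|---|---|---|
| 15% vs 15% | 0 | 0 | about 2.5% |
| 15% vs 20% | 0.0757 | 0.13 to 0.19 | about 4 to 5% |
| 10% vs 15% | 0.0793 | 0.14 to 0.19 | about 4% |
| 15% vs 30% | 0.2224 | 0.39 to 0.54 | about 7 to 11% |

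For example, for 15% vs 30% at r = 0.5: 3.5 × 0.5 × 0.2224 = 0.39.

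**Step 4: the same on the CRP scale.** With the implied SD of 4.48 and the same range of r, a 5-point difference in deaths gives 4.48 × 0.5 × 0.0757 = 0.17 to 4.48 × 0.7 × 0.0793 = 0.25 units. For 15% vs 30% it is 4.48 × 0.5 × 0.2224 = 0.50 to 4.48 × 0.7 × 0.2224 = 0.70 units. The planned difference is 3.

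**Step 5: what ranking death worst costs.** With a true SOFA benefit of 1.5 points, r = 0.7 and 15% deaths in each arm, simulated power is about 33% for the death-ranked test and about 51% for survivors only.

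**The case against.** **The article is a condensation.** It cites a source for the missing-data sentence, which is not at hand and may define an imputation rule. The full protocol or an analysis plan may hold the detail. This stands as far as the absence of an imputation rule goes. It does not rescue the sentence, which states a wrong method and does not merely leave one out, nor the exclusion of deaths, which contradicts it on the face of the text. Imputing a score for a patient who has died would also give that patient a living patient's value.

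**A reader might infer that early death is the main reason for a missing Day-7 value.** The documents do not support that. They give no mortality or attrition rates. They also exclude patients expected to die within 2 days, and they list other routes to loss: a short ICU stay, a change to parenteral nutrition, side effects and withdrawal.

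**A reader might infer that the scores will be biased against the mortality effect.** They may be. The bias needs unequal early deaths that depend on severity, and it is small when the imbalance is small.

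**A reader might conclude that ranking death worst should be the main analysis.** That is one defensible choice of question among several. It brings mortality, already a separate outcome, into the score, and it loses power when deaths are equal (Step 5). If saffron also halved early deaths from 30% to 15%, its power would be about 56% against about 23% for survivors only. Part of that gain is the mortality effect itself, so it does not show that the ranked test is the better test of SOFA.

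**Conclusion.** The point holds as an error in what the plan states. Intention-to-treat is not a way of handling missing values, and excluding patients who die contradicts it. The Day-7 comparisons of the primary biomarkers and of the secondary scores are therefore survivors-only under a label that says otherwise.

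The numerical consequence is conditional. It is nil with equal early deaths, small for a 5-point difference (0.13 to 0.20 SOFA points), and moderate for a doubling from 15% to 30% (0.4 to 0.5 points, with false significance about three to four times nominal). These sizes rest on an assumed SOFA SD of 3.5, correlations of 0.5 to 0.7 and the death rates shown; none is in the documents. The contradiction itself rests on no assumption. It should be corrected before the data are unblinded.

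**What to change.** 1. **Exclusion criteria.** Remove death during the trial as an exclusion. Keep every randomised patient in the analysis set and count all deaths in 28-day mortality.
2. **Statistical methods.** Replace the missing-data sentence. State that Day-7 comparisons of biomarkers and scores are among patients alive at Day 7, and do not call them intention-to-treat. Report deaths before Day 7 by arm beside them. For living patients without a Day-7 value, use multiple imputation from baseline values and the randomisation strata (GCS and age), for scores as well as biomarkers.
3. **Supporting analysis.** Pre-specify a comparison of all randomised patients with death before Day 7 ranked worst, stratified by the randomisation strata, for SOFA, APACHE II, GCS and CRP. Require that it be reported beside the survivors' result.

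The cost is wording and some analysis time. No visit or sample is added. Date of death is needed, and the hospital record and the planned 28-day phone follow-up are natural sources. The ranked analysis is harder to express than a mean difference, mixes mortality into the score, and has less power when deaths are equal. It should therefore support the main comparison and not replace it.
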